#### Child health utility 9D

This 9-item child self-report questionnaire was developed to assess children’s health related quality of life for use in economic evaluation [36].

#### Temperament in middle childhood - self-report questionnaire

The Soothability and Inhibitory Control subscales (16 items) will be used to measure child self-regulation [37].

### Recorded parent-child observation (home assessment)

Direct observation is the gold standard for assessing the nature of parent-child interactions [38, 39]. At the home visit, the participating parent and study child are invited to take part in a free-play activity (5–10 min) and tidy-up task (5 min) using a set of age-appropriate toys and games provided (i.e., LEGO Classic Creative Bricks, Jenga, and animal snap cards). Both tasks are recorded by a researcher using an iPad and will subsequently be coded using the Coding of Attachment-Related Parenting (CARP) scheme [40]. The CARP is a behavioral observation system used to assess two dimensions of attachment-related parenting behaviors (‘Sensitive Responding’ and ‘Mutuality’) rated on a 7-point Likert scale (1 = No evidence; 7 = Pervasive/extreme evidence). *Sensitive Responding* assesses the degree to which the parent promotes their child’s autonomy, shows awareness and sensitivity to the child’s needs and signals, adopts the child’s perspective, and expresses verbal and physical warmth. *Mutuality* reflects the degree to which the parent-child dyad reciprocates positive affectionate behaviors, seeks joint engagement in an activity, maintains shared attention and affect sharing, and maintains physical proximity in interactions. Interrater reliability will be assessed for 10–20% of the participants.

### Parent-report questionnaire (home assessment or online)

Parents are invited to complete a questionnaire on an iPad using the REDCap application during the time that the researcher is conducting the direct child assessment in the home visit. The questionnaire takes parents about 30 min to complete, and consists of 9 sections, asking about parent characteristics (5 items), the study child’s early education experiences (4 items) and formal schooling (9 items), child behavior and development (47 items), child health and wellbeing (32 items), parenting and parent-child interactions (27 items), parent health (20 items), the home environment (11 items), and parent and family demographic information (15 items). Refer to Table 2 for more information regarding these measures.

### Data linkage

Data linkage to state and federal government datasets will be undertaken. Separate consent is requested from parents for each aspect of data linkage.

#### School entrant health questionnaire

This measure is completed by parents of children in government schools in the State of Victoria in Australia at school entry when children are approximately 5 years old [41]. The questionnaire records parents’ concerns and observations about their child’s health and wellbeing, and comprises a number of validated measures, including the Strengths and Difficulties Questionnaire [42] and the Parental Evaluation of Developmental Status [43]. The measure also has questions on speech and language, service use, and family issues and stressors.

#### English online interview

Teachers in Victorian government schools are mandated to assess all students at the beginning of their ‘Preparatory’ or ‘Foundation’ year (age 5) using the English Online Interview, to assess students’ reading, writing and speaking, and listening skills. The assessment consists of a one-to-one interview between a teacher and a student using purpose-developed texts and resources [44]. During the interview with the child, teachers enter scores directly into the online system, where the scores are automatically aggregated and converted to a scale score based on the Victorian Curriculum.

#### National Assessment Program – Literacy and numeracy (NAPLAN)

NAPLAN is an annual national assessment conducted for all Australian children in Years 3, 5, 7 and 9 of school. It is designed to assess children’s skills in a variety of domains including reading, numeracy, spelling, punctuation and grammar [45]. In the current study, we have approval from the Victorian Curriculum and Assessment Authority to link to NAPLAN data collected in Years 3 (age 8) and 5 (age 10).

### Teacher-report questionnaire (online)

Separate consent is requested from parents to allow research staff to contact the child’s current school teacher. The 15-min teacher questionnaire is administered online using the REDCap web application. The questionnaire consists of six sections asking teachers about the school and the child’s year level and classroom (13 items), the child’s and their family’s engagement with the school (10 items), the child’s academic performance (18 items), and social and behavioral development (31 items), the teacher-child relationship (15 items), and the teachers’ level of experience and the school environment (12 items). Items from the questionnaire have been modified from the teacher questionnaire used in the Longitudinal Study of Australian Children when children were 6–7 years of age.

To address Aim 3, we will use the rich process data collected during the original EHLS. We will test whether condition intensity (with vs. without home coaching), dosage (number of sessions attended), and parent engagement in the program sessions influence child outcomes. Regression analyses will be used to test for potential moderating effects of program-specific factors on the relationship between *smalltalk* exposure and parent and child outcomes. To address Aim 4, we will examine child, parent and environmental factors to determine which children are more or less likely to benefit from *smalltalk.* For example, we will examine the extent to which children with poor self-regulation skills, or from families facing multiple socio-economic disadvantages, show differential benefits from their parents’ participation in *smalltalk*. Regression analyses including interaction terms between intervention and child/family factors will be used to test whether child/family factors moderate intervention effects.

To address Aim 5, we will conduct an economic evaluation of the *smalltalk* program. Costs of *smalltalk* incurred by service providers and families from intervention to 7.5 years of age will be estimated from prospectively recorded data on resources used in the *smalltalk* program and parent-report of children’s use of health, social and educational services up to age 7.5 years. These costs will then be compared to the full range of outcomes detailed above using a cost-consequences analysis, which compares any additional costs of *smalltalk* (compared to controls) to the full range of change in outcomes achieved. Analyses will include extensive sensitivity testing to assess the impact of uncertainty in data and modelling assumptions on results.

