## Methods/design

### Aims

This follow-up study, EHLS at School, is focused on the toddler cohort who participated in the facilitated playgroup intervention arm. The decision to limit the school-age follow-up to the toddler cohort was required by resource availability that limited follow-up to one intervention arm of the EHLS. Findings from the EHLS indicated that substantive gains from the *smalltalk* intervention were observed in the toddler trial (parents of toddlers 12–36 months), compared to the infant cohort where gains were not maintained. The study aims are to:investigate the effects of the toddler parenting program *smalltalk* on children’s school readiness, social and emotional development, and academic functioning;investigate whether initial gains in parent-child interactions and the home environment are maintained to age 7.5;identify the program attributes (program intensity, quality and timing) associated with gains in parent-child interactions, the home environment and child outcomes;examine whether the benefits of *smalltalk* are affected by individual child and family factors such as self-regulation, and parent and family contextual factors; anddetermine the financial, health and education costs and cost-effectiveness of *smalltalk*.

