### Outcome measures

To address Aims 1 and 3–5, assessed child outcomes include school readiness, child socio-emotional development, language, mental health, self-regulation and physical health, and academic functioning. To address Aim 2, the home environment and parent-child interactions are assessed. Table 1 provides a summary of domains assessed across the EHLS and EHLS at School studies, while Table 2 provides a detailed summary of key measures included in EHLS at School.

**Table 1 Tab1:** Measurement domains assessed in the EHLS and the EHLS at School studies

Domain	Outcome	Data collection method	EHLS			EHLS at School		
			Pre	Po	FU	5y	7.5y	8-10y
*Child and Parent Outcomes*								
Child language and academic	Language, communication	PQ DA DL	✓	✓	✓	✓	✓	✓
	School readiness, English skills	DL				✓		
	Academic skills	TQ DL					✓	✓
Child socio-emotional and general development	Fine motor skills	PQ	✓	✓	✓			
	Personal-social skills	PQ	✓	✓	✓			
	Developmental status	DL				✓		
	Mental health problems, quality of life	PQ CQ TQ DL				✓	✓	
	Social skills	PQ					✓	
	Self-regulation	PQ					✓	
Parenting and home environment	Parent-child interaction	DA	✓	✓	✓		✓	
	Parenting irritability, warmth, consistency, self-efficacy, verbal responsivity	PQ	✓	✓	✓		✓	
	Home learning activities; home literacy environment	PQ	✓	✓	✓		✓	
*Intervention Experiences*								
*smalltalk* exposure	Number of sessions attended, parent engagement, content exposure	Adm		✓				
Other services	Number and type of sessions attended	PQ					✓	
*Covariates*								
Child	Health and disability, temperament	PQ TQ	✓	✓	✓		✓	
Parent	Mental health, quality of life	PQ	✓	✓	✓		✓	
Family	Demographics, family structure, stressful events, social support	PQ	✓	✓	✓		✓	
Services	Use of educational services and child care	PQ	✓	✓	✓		✓	

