Self-regulation	Approaches to Learning Scale [47] (6 items) assesses children’s eagerness to learn, interest in a variety of things, creativity, persistence, concentration and responsibility, and is rated on a 4 point scale from ‘Never’ to ‘Very often’ or rated as ‘No opportunity to observe this behavior.’	Parent questionnaire (7.5 years); Teacher questionnaire (7.5 years)
	Soothability and Inhibitory Control subscales from the Temperament in Middle Childhood Questionnaire [48] (16 items) assesses children’s rate of recovery from peak distress, excitement, or general arousal, and their capacity to plan and to suppress inappropriate approach responses under instructions or in novel or uncertain situations.	Parent questionnaire (7.5 years)
Quality of life	The Child Health Utility 9D [36] assesses children’s health-related quality of life using 9 questions rated on a 5-point scale. This measure was developed for the use in cost utility analysis (i.e., economic evaluation).	Child assessment (7.5 years)
Physical health	Child global health [49] (1 item) is rated on a 5-point scale from 1 = ‘Excellent’ to 5 = ‘Poor’.	Parent questionnaire (7.5 years)
	Child Health History (3 items) asks parents about hospital stays over past 12 months; current presence of 10 health problems, e.g., ‘wheezing or asthma’; ‘snoring or difficulty sleeping’; and whether ever diagnosed or treated for psychological disorder.	Parent questionnaire (7.5 years)
	Use of health services (1 item) asks parents whether they have used specific health services for their child (e.g., family doctor; Pediatrician; psychological services; dentist), and the cost to the family per visit.	Parent questionnaire (7.5 years)
*Parent-Child Relationship*		
Parent-child interactions	The Sensitive Responding and Mutuality subscales of the Coding of Attachment-Related Parenting scheme [40] assesses attachment-related parenting behaviors rated on a 7-point Likert scale 1 = ‘No evidence’; 7 = ‘Pervasive/extreme evidence’.	Direct child assessment (7.5 years)
Parenting	Parenting warmth [49] (6 items) is rated on a 5-point scale, e.g., “Thinking about the last 6 months, how often do you… hug or hold your child?”	Parent questionnaire (7.5 years)
	Parenting irritability [49] (5 items) is rated on a 5-point scale, e.g., “Thinking about the last 4 weeks, how often have you… lost your temper with your child?”	Parent questionnaire (7.5 years)

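### Aim 4 names child self-regulation as an effect moderator, but the only measures so labelled are taken at 7.5 years and are also outcomes, so an interaction with them cannot reliably show which children benefit

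*Protocol article*

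**What the plan says.** The Aims section asks, as Aim 4, whether the benefits of smalltalk "are affected by individual child and family factors such as self-regulation, and parent and family contextual factors". Self-regulation is the only individual child factor named there, and the Background gives it as the example for the differential-susceptibility question. The Statistical analyses section repeats it: "we will examine the extent to which children with poor self-regulation skills, or from families facing multiple socio-economic disadvantages, show differential benefits". The method is stated as "Regression analyses including interaction terms between intervention and child/family factors will be used to test whether child/family factors moderate intervention effects".

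The Outcome measures section says that for Aims 1 and 3 to 5, which include Aim 4, "assessed child outcomes include school readiness, child socio-emotional development, language, mental health, self-regulation and physical health, and academic functioning". Table 1 puts self-regulation under child and parent outcomes with one tick, at 7.5 years. Table 2 gives two instruments: the Approaches to Learning Scale, by "Parent questionnaire (7.5 years); Teacher questionnaire (7.5 years"), and the "Soothability and Inhibitory Control subscales from the Temperament in Middle Childhood Questionnaire", by parent report at 7.5 years. The self-report form of those subscales belongs to the direct child assessment at the 7.5-year home visit.

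A separate covariate row in Table 1, "Health and disability, temperament", is ticked at Pre, Post, 32-week follow-up and 7.5 years. No section connects it to Aim 4.

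**The concern.** A moderator should describe the child before the programme could act. Here the named child moderator has no measure under that label until years after the programme ended, and the study itself treats it as something smalltalk might improve. A child whose self-regulation improved because of smalltalk would be classed at 7.5 years with children who never had difficulty. Treated and untreated children with the same 7.5-year score then need not have been alike at baseline, and moderation becomes mixed with mediation.

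The error can run either way: real differential benefit may be diluted, or apparent differential benefit may be created. This matters because the article intends its results to help target early intervention at the children who gain most.

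**Working it through.** **Timing.** Baseline age was 12 to 36 months and assessment is at 7.5 years. The gap is 7.5 - 3 = 4.5 years to 7.5 - 1 = 6.5 years.

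**Passages side by side.** Self-regulation is the moderator in Aim 4 (Aims; Statistical analyses). It is an outcome for Aims 1 and 3 to 5 (Outcome measures; Table 1). It is measured only at 7.5 years (Tables 1 and 2; child self-report section). There is no stated figure to reproduce.

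**Illustration.** All parameters below are assumptions except the group sizes, 212 standard and 455 smalltalk, which are those in the Power calculation section.

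Let S0 be baseline self-regulation (mean 0, SD 1), S1 the 7.5-year score, T exposure (0 or 1) and Y the outcome:

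- S1 = 0.6·S0 + 0.8·e + T·(a + b·S0), with e standard normal, so S1 has correlation 0.6 with S0 if untreated
- Y = 0.4·S0 + 0.3·S1 + noise (variance 0.6) + T·(g + h·S0)

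The interaction with S0 is 0.3·b + h.

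For the interaction with S1, the slope of S0 on S1 is 0.6 in controls and k = (0.6 + b)/[(0.6 + b)² + 0.64] in the treated. The S1 interaction is therefore (0.4 + h)·k - 0.4 × 0.6.

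| Scenario | a, b, g, h | S0 interaction | k | S1 interaction |
|---|---|---|---|---|
| 1. No effect on self-regulation | 0, 0, 0.25, 0 | 0 | 0.600 | 0 |
| 2. Uniform shift | 0.3, 0, 0.15, 0 | 0 | 0.600 | 0 |
| 3. True moderation | 0.3, -0.3, 0.15, -0.2 | -0.09 - 0.20 = -0.29 | 0.3/0.73 = 0.411 | 0.2 × 0.411 - 0.24 = -0.158 |
| 4. No moderation, mild differential change | 0.3, -0.3, 0.15, 0.09 | -0.09 + 0.09 = 0 | 0.411 | 0.49 × 0.411 - 0.24 = -0.039 |
| 5. No moderation, steep differential change | 0.3, -0.5, 0.15, 0.15 | -0.15 + 0.15 = 0 | 0.1/0.65 = 0.154 | 0.55 × 0.154 - 0.24 = -0.155 |

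Simulated means over 2,000 runs agree: 0.002, 0.001, -0.159, -0.037 and -0.157. The shares of runs with |t| > 1.96 for the interaction were:

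| Scenario | With S0 | With S1 |
|---|---|---|
| 1 | 4.2% | 5.1% |
| 2 | 4.8% | 5.4% |
| 3 (power) | 99.0% | 59.2% |
| 4 (false positive) | 5.9% | 7.2% |
| 5 (false positive) | 5.1% | 47.3% |

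In scenario 2 the interaction is undistorted, but the treatment coefficient falls from 0.24 to 0.08, because part of the benefit runs through self-regulation and is adjusted away.

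**How much of scenario 3 is post-treatment change?** If smalltalk left self-regulation unchanged (a = b = 0) and h = -0.29, the S1 interaction would be 0.6 × (-0.29) = -0.174. So 0.290 - 0.174 = 0.116 of the total loss of 0.290 - 0.158 = 0.132, or 88%, is plain attenuation from using an imperfect proxy. The remaining 12% comes from the programme changing the moderator.

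**The case against.** The strongest reply is that the article does not say the 7.5-year score will be the moderator. The Aim 4 sentence is introduced as an example and gives no instrument, wave or cut-off. Two of the self-regulation subscales come from a temperament questionnaire, and child temperament was collected at Pre, so a pre-intervention version is compatible with the text. A condensed article may leave that choice to a fuller document. This stands as far as it goes: a reader might infer that the plan commits to the 7.5-year score, and it does not. But the article names the moderator, offers only 7.5-year measures under that name, calls it an outcome for the same aim, and gives baseline temperament no role in Aim 4. Followed as written, it leads to the post-treatment measure.

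A second reply is that bias is conditional. That also stands. Scenarios 1 and 2 show no distortion of the interaction and scenario 4 very little. The study cannot assume itself into those cases, however, since it lists self-regulation among the outcomes smalltalk may change.

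A third reply is that toddler temperament is a proxy too and would also attenuate moderation. This is correct. The article does not describe the Pre temperament instrument, so temperament cannot be credited with recovering the full effect. Its advantage is that the programme cannot have altered it.

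**Conclusion.** The point holds as a flaw in how one named moderator in one of five aims is set out. An interaction between smalltalk and self-regulation measured at 7.5 years cannot reliably identify which children were more likely to benefit.

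The size is unknown. It depends on how far smalltalk changes self-regulation, on whether that change differs by baseline level, and on the correlation between toddler and school-age self-regulation. The documents give none of these. Under the assumed values the consequences range from no distortion to a loss of power from 99% to 59%, or a false-positive rate of 47%.

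A reader might infer a much larger and more definite harm. Suppose only the lowest quarter at baseline benefits, by 0.50 SD, with a baseline to 7.5-year correlation of 0.3 to 0.5 and a programme effect on their self-regulation of 0.25 to 0.5 SD. Splitting at 7.5 years can then show a difference between strata of only 0.07 to 0.13 SD, a loss of 74% to 86%. That should not be read as the cost of conditioning on a consequence of treatment. With the programme's effect on self-regulation set to zero, the bivariate normal model gives 0.5 × (0.380 - 0.207) = 0.087 at correlation 0.3 and 0.5 × (0.481 - 0.173) = 0.154 at 0.5, which are losses of 83% and 69%. Most of the figure is proxy attenuation under assumed correlations.

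Nor does the point undermine Aim 4 as a whole. Multiple socio-economic disadvantage, the other example, is unaffected if taken from enrolment data. Whether exposure or allocation should define the groups is a separate question.

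**What to change.** State that Aim 4 moderators are restricted to variables measured at Pre. Table 1 shows candidates already collected: child temperament (as an imperfect proxy for self-regulation), parent mental health, stressful events, and demographics including social risk at enrolment. Name the variable used for each. Analyse 7.5-year self-regulation as an outcome. If an interaction with it is still wanted, label it exploratory and non-causal.

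The cost is a change of wording and variable choice, with no new data collection. The drawback is that toddler temperament measures self-regulation less directly than the school-age scales and may itself weaken any moderation found, so a null result with it should be reported with that caution.

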### Progress

As of May 2017, the research team has attempted contact with all eligible participants (*n* = 990), of which 637 (64%) have agreed to further contact when their child reaches the eligible age, and 128 (13%) have declined or ‘passively refused’ (i.e., maximum attempts to contact reached with no participation). Further attempts to make contact will continue for the remaining 225 (23%) participants. Assessments have been completed for 373 participants. Of these, 16 participants did not complete the home assessment but instead provided data in the form of the online parent and teacher questionnaires, and consent for data linkage. So far, more than 90% of parents have consented to completion of the online teacher questionnaires, and to data linkage. Based on completed fieldwork, we anticipate a final sample with complete child and parent data of between 60% and 65% of the initial sample.

## Discussion

The original EHLS was ground breaking in a number of ways. It was the first Australian study and one of only a few internationally to employ rigorous program development and research methods to examine the effectiveness of a parent-focused early home learning intervention. Key strengths included: (1) a 9-month development process to ensure the evidence-informed intervention strategies were appropriate to target parents and could be delivered reliably within the existing service system; (2) application of a cluster-randomized controlled trial design, with strategies to minimize cross-condition contamination (site-based allocation to condition; staff trained in one condition only) and researcher bias (blinding of field/coding staff); and (3) the collection of data from a large sample, with excellent participation rates and retention over time, enhancing confidence in the generalizability of study findings [25].

The EHLS has already had a significant influence on early childhood policy in Victoria, Australia. On the basis of the evidence of *smalltalk*’s short-term benefits to socially and economically disadvantaged families, the State Government has invested in its state-wide roll-out with potential for widespread benefits to vulnerable children. While the EHLS findings are highly promising, they leave unanswered the question of whether *smalltalk* results in sustained changes in the home environment and enhancement of children’s capabilities by the time they enter school.

Internationally, economic evaluations of early life interventions are scarce, particularly those based on long-term follow-ups of rigorously implemented randomized controlled trials [28]. Despite this, there is evidence that early interventions which result in long-term gains for children have substantial economic benefits at a societal level [28]. We have good reason to expect that the modest short-term gains seen in the EHLS could translate into sizeable economic benefits if sustained over time. Our combined outcomes data and economic evaluation will provide important new knowledge to underpin the development of service systems effectively targeted to the needs of disadvantaged families.

